### Eligibility criteria

The inclusion criteria are defined as follows: (1) Patients scheduled for bilateral orthognathic surgery (including Le Fort I osteotomy and bilateral sagittal split osteotomy); (2) male and female patients aged 18 to 64 years; (3) American Society of Anesthesiologists (ASA) physical status I-II; (4) patients informed about the study protocol with signed written consent.

The exclusion criteria comprise: (1) Presence of local scars or infections in acupuncture areas; (2) limb absence or peripheral nerve injury; (3) body mass index (BMI) > 30 kg/m^2^; (4) history of substance abuse; (5) history of central nervous system disorders or psychiatric conditions; (6) requirement for postoperative intensive care unit (ICU) transfer; (7) current participation in other clinical trials.

Participants meeting any of the following criteria post-enrollment will be withdrawn: (1) Surgical cancellation or conversion to a single-jaw procedure; (2) inability to tolerate acupuncture therapy; (3) premature removal (<24 h) of thumb-tack needles for any reason. All withdrawal cases must be thoroughly documented. Participants who have received the intervention will complete follow-up assessments. No efficacy analyses will be performed for withdrawn cases.

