### The principle of randomness

This study will utilize computer-generated block randomization with a total sample size of 216 cases divided into 54 blocks, each containing 4 cases. These blocks are equally allocated to two groups, with sequences randomly arranged within each block. Allocation details will be secured in opaque, sealed envelopes. After obtaining signed informed consent, the acupuncturist administering the intervention will access the randomization sequence through the Random.org website (https://www.random.org/) and then open the corresponding sealed envelope to access group assignment details.

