### Blind method

This trial employs a sham-controlled design. The true stimulation group receives intervention at the PC6 acupoint, while the sham stimulation group undergoes stimulation at a non-acupoint site on the forearm. A designated acupuncturist performs thumb-tack needle insertion at predetermined locations according to group assignment, followed by application of an opaque white sterile patch to secure the device and maintain blinding. The same practitioner removes all thumb-tack needles 24 h post-intervention. Both needle insertion and removal procedures are exclusively performed by the assigned acupuncturist. A trained follow-up coordinator conducts postoperative assessments.

To assess the integrity of participant blinding, within 24 h postoperatively, participants will be asked to guess whether the stimulation was received at a real acupoint (PC6) or at a sham acupoint (non-acupoint). Responses will be recorded on the case report form (CRF), and the proportion of correct guesses will be summarized.

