### Intervention

Upon entering the operating room, the acupuncturist generates a randomization sequence via the Random.org website (https://www.random.org/) to access the corresponding sealed envelope containing group allocation details. Before induction of anesthesia, the acupuncturist applies the assigned thumb-tack devices bilaterally according to the randomized allocation. Both groups receive two thumb-tack devices: a real needle (0.25 mm × 2.0 mm, disposable sterile press needles) and a sham needle with identical appearance but no needle tip. In Group A, the real device is bilaterally applied to the PC6 acupoint – located three finger breadths proximal to the wrist crease between the palmaris longus and flexor carpi radialis tendons – while the sham device is bilaterally positioned at the non-acupoint site six finger breadths proximal to the wrist crease and 2 cm ulnarly. Group B receives the inverse configuration, with sham stimulation bilaterally at PC6 and real stimulation bilaterally at the non-acupoint site. The sham site maintains a 3 cm radius free of established acupoints to prevent collateral stimulation (Figure 3). No deliberate De Qi sensation is elicited during application. Opaque sterile patches will be applied to both intervention sites to conceal the allocation information (Figure 4), with devices remaining *in situ* for 24 postoperative hours. All acupuncture-related procedures are performed in strict accordance with aseptic principles to minimize the risk of infection. Both groups receive standardized PONV prophylaxis per guidelines (18): dexamethasone 5 mg, palonosetron 0.075 mg, propofol target-controlled infusion (TCI) 0.5 μg/mL, and pharyngeal packing.

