All patients receive intravenous cefuroxime axetil 1.5 g immediately post-induction, with an equivalent prophylactic dose administered 3 h intraoperatively. Axillary temperature maintenance ≥36 °C is ensured using forced-air warming blankets as required. Flurbiprofen 50 mg is administered intravenously 6–7 min prior to surgical skin incision to prevent inflammatory pain. Local infiltration anesthesia with 4% lidocaine containing 1:100,000 epinephrine is applied to both mandibular and maxillary regions. Pharyngeal packing with sterile gauze is implemented to minimize blood ingestion. Controlled hypotension during Le Fort I osteotomy is maintained at a mean arterial pressure (MAP) 50–65 mmHg through combined administration of sevoflurane, metoprolol, and urapidil. Sufentanil 5 μg combining with palonosetron 0.075 mg are administered 30 min prior to surgical closure as preemptive analgesic and antiemetic therapy. Postoperative analgesia was provided via patient-controlled intravenous analgesia (PCIA) using a solution containing sufentanil 100 μg and flurbiprofen 200 mg, diluted with normal saline to a total volume of 100 mL. The pump was programmed with a basal infusion rate of 2 mL/h, a bolus dose of 2 mL, and a lockout interval of 15 min. Neuromuscular blockade reversal with sugammadex is selectively administered based on the patient’s muscle strength recovery. Rescue therapy for refractory PONV consists of intravenous droperidol 1 mg. Supplemental tramadol 100 mg IV is administered if Numerical Rating Scale (NRS; 0 = no pain, 10 = worst pain imaginable) scores exceed 3 points despite three consecutive effective PCIA boluses, with repeat dosing permitted as clinically indicated.

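### Needle removal is timed from two different origins, and the under-24-hour withdrawal rule that decides who is analysed names no origin

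*Protocol article*

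**What the plan says.** The protocol article gives the timing in several places.

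- **Intervention** fixes the start: "Before induction of anesthesia, the acupuncturist applies the assigned thumb-tack devices bilaterally according to the randomized allocation". It keeps the devices in place "for 24 postoperative hours".
- **Blind method** instructs the person who takes the needles out: "The same practitioner removes all thumb-tack needles 24 h post-intervention". It reserves both insertion and removal for the assigned acupuncturist.
- **Abstract (Methods)** also counts from surgery, but words the 24 h as both a maximum and a minimum.
- **Table 1** times its Intervention column before induction, gives the operation its own column, and ticks PC6 stimulation through the 6–24 h postoperative column. It does not state an end time.
- **Eligibility criteria** lists among the withdrawal reasons "premature removal (<24 h) of thumb-tack needles for any reason", with no starting point for the 24 h. It adds "Participants who have received the intervention will complete follow-up assessments" and then "No efficacy analyses will be performed for withdrawn cases".
- **The principle of randomness** shows that the person who applies the needles knows the allocation: "the acupuncturist administering the intervention will access the randomization sequence" and then opens the envelope.

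**The concern.** There are two linked problems.

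The first is treatment exposure. If 24 h runs from application, stimulation stops before the 24 h postoperative primary window closes. The lost hours fall at the end of the 6–24 h interval. The Discussion faults earlier studies for not keeping stimulation going after surgery, so this is the part of the regimen meant to set the trial apart.

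The second is the analysis population. An event after randomisation, measured against a clock with no stated zero, decides whether a randomised participant enters the efficacy analysis. If the withdrawal rule counts from the end of surgery, a participant treated exactly as Blind method directs is withdrawn. If it counts from application, the same participant stays in. The removals are made by someone who knows the allocation. Nothing suggests misuse, but an unclear threshold in those hands need not act equally in the two arms.

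**Working it through.** **What 'post-intervention' means.** The term is not defined. Table 1 puts the intervention before induction, separate from the operation. The principle of randomness speaks of the acupuncturist administering it, and the section describing needle placement carries the word as its heading. On that usage, Blind method counts from application. A looser postoperative sense is possible, because Ethics and dissemination plan uses the word for surgery.

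**Size of the gap.** Let T be the time from application to the end of surgery. Under the literal Blind method rule:

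- removal time = 24 − T hours postoperatively
- uncovered share of the 24 h window = T/24
- uncovered share of the 6–24 h interval = T/18

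The document gives no value for T. Anesthetic management gives all patients a first cefuroxime dose after induction, "with an equivalent prophylactic dose administered 3 h intraoperatively". This implies operations planned to reach about 3 h; that is an inference, not a stated duration. The 200-minute subgroup cut in Statistical analysis is compatible with it. The upper end of 8 h is an assumption.

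| T (h) | Removal (h postoperatively) | T/24 | T/18 |
|---|---|---|---|
| 3 | 21 | 12.5% | 16.7% |
| 4 | 20 | 16.7% | 22.2% |
| 6 | 18 | 25.0% | 33.3% |
| 8 | 16 | 33.3% | 44.4% |

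**The plan's own sample size.** Sample size estimation uses p1 = 0.610, p2 = 0.427, one-sided α = 0.05 and power 0.80. Its formula with z values 1.645 and 0.84 gives 91.02, rounded up to 92 per group, as stated. Then 92/0.9 = 102.2, so 103, or 104 in blocks of four. Nothing in this point changes that figure.

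**Cost of keeping early removals in the analysis.** Power of the two-proportion z-test against zero difference, pooled variance under the null:

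power = Φ{[(p1 − p2)√n − zα√(2p̄(1 − p̄))] / √(p1(1 − p1) + p2(1 − p2))}

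With n = 108 per group (216 enrolled) and p2 = 0.427: (0.183 × 10.392 − 1.645 × 0.7066)/0.6947 = 1.064, so power is 0.856.

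Now assume a fraction f of group A is removed early and gets no benefit at all: p2 = 0.427(1 − f) + 0.610f.

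- f = 5%: p2 = 0.436, difference 0.174
- f = 10%: p2 = 0.445, difference 0.165

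| Per group | Scenario | One-sided 0.05 | One-sided 0.025 |
|---|---|---|---|
| 108 | no early removal | 0.856 | 0.772 |
| 108 | 5% diluted | 0.823 | 0.728 |
| 108 | 10% diluted | 0.785 | 0.681 |
| 97 | 10% excluded from each arm | 0.822 | 0.726 |
| 104 | no early removal | 0.845 | 0.756 |
| 104 | 10% diluted | 0.772 | 0.665 |
| 93 | 10% excluded from each arm | 0.807 | 0.708 |

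The 0.025 column is shown because the one-sided 97.5% interval in Statistical analysis implies that level.

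**The case against.** The intended rule can largely be recovered. Intervention is the section that specifies treatment, and it counts from surgery. So does the Abstract, and Table 1 fits. Blind method is the one outlier, in a section mainly about who handles the needles. Calling a removal premature implies earlier than planned, which points back to the postoperative 24 h. The full protocol may also define the origin. On this view the defect is loose wording. The shares above are clock time rather than effect, T is inferred or assumed, and excluding withdrawn participants is a separate issue from the time origin.

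Much of this stands. The postoperative origin is the likelier intention, the loss of exposure depends on staff following Blind method literally, and its effect cannot be quantified. The 5% and 10% early-removal rates are assumptions: the 10% in Sample size estimation is total attrition. The power figures test against zero difference, not the 0.183 margin that Statistical analysis names. Documentation of every withdrawal and a separate follow-up coordinator are real safeguards.

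It does not dispose of the point. Blind method is the working instruction to the person who removes the needles and should not need interpreting. The withdrawal rule is a stated rule, not an omitted detail, and its missing origin decides who is analysed. For that reason the two issues belong together here.

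**Conclusion.** The concern holds and should be fixed, though it is not fatal. The two removal instructions conflict on the article's main usage of 'intervention', and the withdrawal rule inherits the ambiguity. Followed literally, Blind method has the needles out no later than 21 h after surgery if T is at least 3 h, so at least 3 h of the primary window is uncovered; at an assumed 8 h, a third of the window is. Because both arms are affected alike, that loss would weaken the contrast rather than bias it. The route to bias is the exclusion after randomisation, whose trigger is ambiguous and whose execution rests with an unblinded person; its size cannot be derived from the document. Confidence is medium, because a postoperative reading of Blind method is possible and T is not stated.

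**What to change.** 1. In Blind method, state that needles are removed no earlier than 24 h after the end of surgery, in line with Intervention.
2. In Eligibility criteria, define premature removal from the same origin: earlier than 24 h after the end of surgery.
3. Record application and removal times on the case report form.
4. Keep participants with early removal in the primary analysis as randomised. Those who received the intervention already complete follow-up, so the outcome data will exist. Let early removal define only a per-protocol sensitivity set.

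Items 1 to 3 cost two text edits and two form fields. Item 4 costs some dilution. If 10% of group A were removed early with no benefit, the expected difference falls from 18.3 to 16.5 points. Power at 108 per group then falls from 86% to 79% at one-sided 0.05, or from 77% to 68% at 0.025. Excluding 10% from each arm would itself lower power to 82% or 73%, so the net price against the present rule is about 4 to 5 points. If only 5% were removed early, power as randomised would be 82% or 73%.

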### Emergency unblinding

Following acupoint stimulation, immediate emergency intervention must be initiated if patients develop acute allergic reactions, severe bradycardia (heart rate <40 bpm), profound hypotension (systolic blood pressure <70 mmHg), acute respiratory distress, or cardiac arrest. Participants meeting these criteria will be immediately withdrawn from the trial. The principal investigator will disclose the allocation details to the treatment team and submit a formal report to the ethics committee after stabilization of the patient’s condition. The emergency unblinding procedure is detailed in Figure 2.

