### Anesthetic management

All patients will undergo standardized preoperative fasting, 8 h for solids, and 3 h for clear fluids. Continuous monitoring will include non-invasive blood pressure, electrocardiogram (ECG), pulse oximetry (SpO_2_), axillary temperature, end-tidal carbon dioxide (EtCO_2_), inspired anesthetic concentrations, and hourly urine output measurement. To enhance external validity and minimize confounding, anesthetic management will be standardized. Anesthesia induction will be achieved with dexamethasone 5 mg IV, propofol TCI 3–4 μg/mL, sufentanil 0.2–0.4 μg/kg, and rocuronium 0.6–0.8 mg/kg. Nasotracheal intubation under direct laryngoscopic guidance initiates mechanical ventilation using a lung-protective strategy: FiO2 40–60%, tidal volume 6 mL/kg predicted body weight, with EtCO_2_ maintained at 35–45 mmHg through respiratory rate adjustment. Maintenance combines propofol TCI 0.5 μg/mL, sevoflurane 1.5–2.5% (minimum alveolar concentration ≥1.0 MAC), remifentanil 0.1–0.2 μg/kg/min, and supplemental rocuronium boluses. Invasive arterial pressure monitoring via radial artery catheterization will be established in the non-dominant upper extremity.

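### Participants with an intraoperative emergency such as SBP <70 or HR <40 are withdrawn after treatment and, on the natural reading, dropped from the primary comparison

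*Protocol article*

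**What the plan says.** The Intervention section fixes the timing: "Before induction of anesthesia, the acupuncturist applies the assigned thumb-tack devices bilaterally according to the randomized allocation". Everything that happens in theatre is therefore post-randomisation and post-treatment.

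The Emergency unblinding section lists five events after stimulation. Two are haemodynamic thresholds, "severe bradycardia (heart rate <40 bpm), profound hypotension (systolic blood pressure <70 mmHg"; the others are acute allergic reaction, acute respiratory distress and cardiac arrest. Its consequence is: "Participants meeting these criteria will be immediately withdrawn from the trial". The procedure is said to be detailed in Figure 2, which is not shown.

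The Eligibility criteria section has its own withdrawal rule, "Participants meeting any of the following criteria post-enrollment will be withdrawn", followed by three reasons: cancelled surgery or conversion to a single-jaw procedure, intolerance of the acupuncture, and needle removal before 24 h whatever the reason. The emergencies are not listed. The paragraph ends with two statements about withdrawn participants: "Participants who have received the intervention will complete follow-up assessments" and "No efficacy analyses will be performed for withdrawn cases".

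The Anesthetic management section plans low pressure: "Controlled hypotension during Le Fort I osteotomy is maintained at a mean arterial pressure (MAP) 50–65 mmHg". It also provides continuous measurement: "Invasive arterial pressure monitoring via radial artery catheterization will be established in the non-dominant upper extremity".

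**The concern.** The Emergency unblinding section uses the same word, withdrawn, as the Eligibility criteria section, whose bar on efficacy analysis carries no qualifier. Taken together they remove randomised, treated participants from the 24 h PONV comparison because of something that happened after treatment. The groups compared are then no longer those that randomisation formed.

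Two features make the rule looser than a safety rule needs to be. First, the visible text asks for no link to the needles and no minimum duration, and it makes no exception for deliberately lowered pressure. With an arterial line in place, brief readings below 70 would be seen. Second, treated participants are to complete follow-up, so outcomes would often be collected and then discarded.

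Those excluded may also differ in prognosis. No statement ties SBP <70 or HR <40 as such to PONV, but the Background names intraoperative controlled hypotension as an independent PONV risk factor in this surgery, and the Statistical analysis section makes hypotension over 60 minutes a subgroup factor.

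**Working it through.** **1. Does the text lead to exclusion?** There are two routes.
- By inference: an emergency makes the participant withdrawn, and withdrawn cases get no efficacy analysis.
- Directly: if the needles come out during the emergency, removal before 24 h is the third listed withdrawal reason, and the bar applies expressly.

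**2. Overlap with planned hypotension.** Assume SBP = MAP + (2/3) × pulse pressure. Then SBP <70 requires pulse pressure below 1.5 × (70 − MAP).

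| MAP (mmHg) | Pulse pressure needed for SBP <70 |
|---|---|
| 50 | <30 |
| 55 | <22.5 |
| 60 | <15 |
| 65 | <7.5 |

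The overlap is realistic only at the low end of the 50–65 target. The protocol gives no trigger rate.

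**3. Power.** Inputs from Sample size estimation: p1 = 0.610, p2 = 0.427, one-sided alpha 0.05 (Z = 1.645), power 0.80 (Z = 0.84), 10% attrition. The mean rate is 0.5185.

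The plan's own figure first: [1.645 × √(2 × 0.5185 × 0.4815) + 0.84 × √(0.610 × 0.390 + 0.427 × 0.573)]² / 0.183² = (1.645 × 0.7066 + 0.84 × 0.6947)² / 0.0335 = 91.02, rounded up to 92. Then 92/0.9 = 102.2, so 103, and 104 per arm for blocks of four. This reproduces.

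Power = Φ[(0.183 × √n − 1.645 × 0.7066) / 0.6947], with n = (N/2) × (1 − excluded share). The protocol gives two totals, 208 in Sample size estimation and 216 elsewhere, so both are shown.

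| Excluded | N = 208 | N = 216 |
|---|---|---|
| 0% | 84.5% | 85.6% |
| 10% | 80.9% | 82.2% |
| 12% | 80.1% | 81.5% |
| 15% | 78.9% | 80.3% |
| 16% | 78.5% | 79.8% |

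Power is not at risk from a rare event.

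**4. Possible bias.** Suppose there is no true effect, with 104 per arm and 61% PONV in each (0.61 × 104 = 63.44 cases). Exclude ka acupuncture and kc control participants, whose PONV risk is r:

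spurious difference = (63.44 − ka·r)/(104 − ka) − (63.44 − kc·r)/(104 − kc).

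Example with ka = 8, kc = 2, r = 0.8: 57.04/96 − 61.84/102 = 0.5942 − 0.6063 = −0.0121.

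Percentage points; negative favours acupuncture. All splits and values of r are assumptions.

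| Excluded (acupuncture, control) | r = 40% | 61% | 80% | 100% |
|---|---|---|---|---|
| 8, 2 | +1.3 | 0 | −1.2 | −2.5 |
| 2, 8 | −1.3 | 0 | +1.2 | +2.5 |
| 3, 1 | +0.4 | 0 | −0.4 | −0.8 |
| 1, 3 | −0.4 | 0 | +0.4 | +0.8 |
| 5, 5 | 0 | 0 | 0 | 0 |

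With 108 per arm, the 8, 2 row becomes +1.3, 0, −1.2, −2.4. Bias needs both unequal exclusion and a PONV risk among the excluded that differs from the rest.

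**5. Cost of keeping them.** A participant who truly has no 24 h outcome can move an arm's rate by at most 1/104 = 0.96 point (1/108 = 0.93).

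**The case against.** The case against is substantial.

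- **The link is inferred.** The bar on efficacy analysis closes a paragraph about three named reasons, and the Emergency unblinding section is silent on analysis. This stands as a caution, but the bar is worded without restriction and needle removal triggers it directly.
- **Figure 2 is unseen.** It may add conditions, and a participant whose pressure was lowered on purpose may not count as having developed hypotension. This also stands, so the controlled-hypotension overlap is a secondary argument.
- **There may be a tiered scheme.** Adverse events management treats SBP <80 and HR <40 with drugs and monitoring and does not mention withdrawal, which suggests the emergency rule is for graver cases. That does not settle it: HR <40 appears in both sections, every SBP <70 is also below 80, and nothing there returns withdrawn participants to the analysis.
- **The harm is small and undirected.** Both arms receive a real forearm needle, the two haemodynamic thresholds are objective, and the Discussion says anaesthesiologists are blinded. Unequal exclusion would need a haemodynamic effect of needle site, for which the Background offers only a possible influence on sympathetic activity. Even the 8 versus 2 split is small beside the 18.3-point design difference. All of this stands and limits the weight of the point.
- **This is the rarer route.** The exclusion for early needle removal in general is broader. That is so, but it does not make this rule sound.

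**Conclusion.** The concern holds as a point to consider. A stated rule, not an omitted detail, removes randomised and treated participants after randomisation, although the protocol has treated participants complete follow-up. This rests on reading the bar for withdrawn cases as covering emergency withdrawals, which is the natural reading, or on the needles being removed during the event, where the bar applies expressly.

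The frequency is unknown and probably small. Power is not threatened within the 10% attrition allowed. Bias may be nil and has no predictable sign; under the assumed splits it ranges from 0 to about 2.5 points either way. The reason to act is that the exclusion is avoidable at almost no cost.

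**What to change.** **Core change.** Amend Emergency unblinding and Eligibility criteria so that an emergency leads to treatment, and to unblinding or device removal where clinically needed, but not to exclusion. These participants complete the 24 h assessment and are analysed in their randomised group. Needle removal during an emergency must be covered too, or the early-removal criterion would exclude them again. Report the analysis without them as a sensitivity analysis.

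**Optional additions.**
- A rule for those who cannot be assessed, for example after cardiac arrest. One defensible choice: PONV recorded before the event counts as PONV; otherwise count as PONV in either arm, with best-case and worst-case bounds.
- A statement that intended, on-target controlled hypotension is not itself a withdrawal trigger, with Adverse events management aligned.

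**Cost.** Wording in two sections, and in Figure 2 if it repeats the rule, plus a sentence or two for the optional rules. No extra participants or procedures are needed and emergency care is unchanged. The instruction to withdraw from the trial must be reconciled with the existing requirement that treated participants complete follow-up.
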